**Methods:**

VISION, a 24-week, phase 4, prospective, randomized, multicenter, open-label, parallel-group study, will include 3312 Chinese T2DM patients aged ≥18 years who are inadequately controlled (6.5% >HbA1c ≤9%) by metformin (750–1000 mg/day). Eligible patients will be randomized to receive either vildagliptin plus metformin or up-titration of metformin monotherapy (5:1). Patients will also be subgrouped (1:1:1:1) based on their age and body mass index (BMI): <60 years and <24 kg/m^2^; <60 years and ≥24 kg/m^2^; ≥60 years and <24 kg/m^2^; and ≥60 years and ≥24 kg/m^2^.

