## Materials and methods

### Subjects

Male and female Chinese T2DM patients (WHO/IDF criteria [38]) aged >18 years with HbA1c levels ranging between 6.5% and 9.0% and BMI between 22 and 45 kg/m^2^ at visit 1 who have received metformin at a stable dose of 750–1000 mg daily for at least 12 weeks before screening will be enrolled in the study. The patients will be required to maintain their individual eating and exercise habits during the study, and to follow all the study requirements. Written informed consent will be obtained from each patient prior to enrollment. Exclusion criteria for the study are listed in Table 1.

**Table 1 T1:** Exclusion criteria for the VISION study

	
**1.**	Pregnant or lactating women
**2.**	Medical history of following diseases:
	• Type 1 diabetes mellitus or diabetes caused by pancreatic injury or secondary diabetes: Cushing syndrome or acromegaly
	• Acute complications of diabetes: ketoacidosis or non-ketotic hyperosmolar coma within the past 3 months
	• Acute infections within 4 weeks prior to the screening (visit 1) that may affect the efficacy and safety of the study
	• Any obvious diabetic complications such as symptomatic autonomic neuropathy, gastroparesis, worsening hyperglycemia in the absence of any comorbid illnesses, and conditions that may affect blood glucose
	• History of kidney disease or clinical diagnosis of renal insufficiency indicated by serum creatinine ≥132 μmol/L (≥1.5 mg/dL) in males, and ≥123 μmol/L (≥1.4 mg/dL) in females
	• History of a liver disease such as cirrhosis, hepatitis B, or hepatitis C (except carriers) or Alanine transaminase (ALT), aspartate aminotransferase (AST) greater than 2 times the ULN or total bilirubin greater than 2 times the ULN
	• History of acute and chronic pancreatitis
	• Malignant tumor in the past 5 years, including leukemia and lymphoma (except for carcinoma in situ of the skin)
	• Torsades de pointes ventricular tachycardia or persistent, clinically relevant ventricular tachycardia or ventricular fibrillation or second-degree atrioventricular block (Mobitz type I and II) or third-degree atrioventricular block, or QTc prolongation (>500 ms)
	• Myocardial infarction, coronary artery bypass surgery or percutaneous coronary intervention, unstable angina, or stroke within the past 6 months
	• Congestive heart failure requiring medical treatment
**3.**	Fasting plasma glucose >15 mmol/L (>270 mg/dL) at visit 1

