**Figure 1 F1:**
[figure not shown]
Design of the VISION study.

Patients participating in the study will be subgrouped (1:1:1:1) based on their BMI and age into 4 groups: (1) <60 years and BMI <24 kg/m^2^; (2) <60 years of age and BMI ≥24 kg/m^2^; (3) ≥60 years of age and BMI <24 kg/m^2^; and (4) ≥60 years of age and BMI ≥24 kg/m^2^. In each group, patients will be randomized according to the study design. At visit 1, patients meeting the inclusion criteria will be assigned to open-label metformin 500 mg bid for a 4-week lead-in period. At visit 2, patients will be randomized in a ratio of 5:1 to receive either vildagliptin 50 mg bid plus metformin 500 mg bid (Group A) or metformin 500 mg tid (Group B) for the next 4 weeks. From visit 3 to the end of the study, Group A patients will continue to receive the maintenance dose of vildagliptin 50 mg bid plus metformin 500 mg bid, while group B patients will receive metformin 1000 mg bid.

The primary, secondary, and exploratory objectives of the study are shown in Table 2. The study drug will be discontinued if it shows unsatisfactory efficacy at week 12 (i.e., FPG >13.3 mmol/L [240 mg/dL]) confirmed by a repeated measurement in the absence of any concurrent illness. Worsening of glucose levels in the absence of any other explainable concurrent disease or emergency condition that can affect glucose levels, the occurrence of AEs including GI side effects or clinically significant changes in laboratory parameters, or an abnormality that, in the opinion of the investigators, requires immediate withdrawal of treatment, will also lead to the study drug being discontinued. An inexplicable increase in levels of liver enzymes (aspartate transaminase, alanine aminotransferase and total bilirubin) without any clinical signs that is confirmed by a repeat measurement within 3 working days, pregnancy, severe or frequent hypoglycemia (i.e., unexplained hypoglycemic events requiring the assistance of another person or >3 hypoglycemic events within a week), treatment with prohibited concomitant medications, or any other deviation from the treatment protocol will also lead to treatment discontinuation. The reason for a patient discontinuing treatment will be recorded in the case report form.

**Table 2 T2:** Primary, secondary, and exploratory objectives of the VISION study

	
**1.**	**Primary objective:**

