In order to control the overall type I error at alpha = 0.05, a sequential test procedure along with the Hochberg procedure will be employed. Non-inferiority testing for the overall population will be performed first. After achieving non-inferiority for the overall population, non-inferiority testing for the 4 subgroups will then be performed. Secondary efficacy variables include percentages of patients achieving therapeutic goals at the study endpoint: HbA1c ≤6.5%, HbA1c ≤6.5% without GI side effects, and absolute decreases in HbA1c from baseline of ≥1%, ≥0.7%, and ≥0.5%. In the FAS and PPS populations, the percentages of patients achieving the therapeutic goals will be analyzed and compared between treatment groups using the Chi-square test.

To assess the robustness of the results of the primary efficacy analysis, i.e., the change from baseline in HbA1c at 24 weeks, an ANCOVA model with LOCF will be used for the PPS. For the primary and secondary efficacy endpoints, subgroup analyses based on age and BMI will be performed.

Safety analyses will include summaries of AEs, changes from baseline in vital signs, the number of subjects with post-baseline laboratory values that will fall outside predetermined ranges, and the frequency and severity of hypoglycemic events. Adverse events will be summarized by system organ class and preferred terms. Summaries of AEs by severity and by relationship to study drug will also be provided.

The incidence of patients with any GI events will be compared between treatment groups using Fisher’s exact test.

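### The responder and GI-event comparisons use valid but unadjusted tests, giving up some precision that baseline HbA1c and the age/BMI randomization groups could recover at no cost

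*Protocol article*

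**What the plan says.** All references are to the protocol article.

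- **Responder goals (Data analysis).** Five goals are listed: "HbA1c ≤6.5%, HbA1c ≤6.5% without GI side effects, and absolute decreases in HbA1c from baseline of ≥1%, ≥0.7%, and ≥0.5" (percent). For these, in both the full analysis set and the per-protocol set, "the percentages of patients achieving the therapeutic goals will be analyzed and compared between treatment groups using the Chi-square test". No covariate or stratification factor is named.
- **GI events (Data analysis).** "The incidence of patients with any GI events will be compared between treatment groups using" Fisher's exact test, again with no stratification.
- **Randomization (Study design).** Four groups are formed from age (below 60, or 60 and over) and BMI (below 24, or 24 and over). "In each group, patients will be randomized according to the study design"; at visit 2 "patients will be randomized in a ratio of 5:1".
- **Subgroups (Data analysis).** "For the primary and secondary efficacy endpoints, subgroup analyses based on age and BMI will be performed".
- **Entry HbA1c.** Subjects gives "HbA1c levels ranging between 6.5% and 9.0" percent, tied to visit 1. The Discussion gives the same range. The abstract's Methods paragraph has patients "who are inadequately controlled (6.5% >HbA1c ≤9" percent.
- **Visit 2 (Study design, Table 3).** A 4-week lead-in on metformin 500 mg bid comes first. HbA1c is measured at visit 2, and the eligibility check is also marked there.

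**The concern.** The article randomizes within the age/BMI groups and says in its Discussion that obesity and age influence how well antidiabetic therapy works. A patient's starting HbA1c also bears strongly on whether 6.5% is reached. Yet the named tests for the overall binary comparisons use none of this. The planned subgroup analyses give estimates within groups, not a stratified overall estimate, and they cover efficacy endpoints only.

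Precision matters here because 5:1 allocation leaves only one sixth of patients in the metformin arm. The responder and GI comparisons also inform the hypothesis, stated in the abstract, that the combination is better tolerated.

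A second issue concerns the two goals built on 6.5%. The entry range as given in Subjects does not exclude 6.5%, and the lead-in dose is an increase for anyone who enters on 750 mg/day. Some patients may therefore be at goal before randomized treatment starts. The article gives no rule for them.

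**Working it through.** **Scale.** The article states no power, event rate or sample size for the responder or GI tests, so there is no figure of its own to reproduce. Its sample size serves only as a scale:
- Randomized: 3312 × 5/6 = 2760 and 3312/6 = 552.
- Evaluable: 4 × 690 = 2760, that is 2300 and 460.

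**Step 1: validity and precision of the crude responder test.** The assumptions are illustrative and not from the article:
- 2300 vs 460 evaluable patients, exactly 5:1 in each group.
- Baseline HbA1c with mean 7.3 and SD 0.6, values outside 6.5–9.0 set to the nearest limit.
- Residual SD 0.8, and about 30% of the metformin arm at or below 6.5%.
- Two-sided 5% level, 1500 simulated trials per setting.

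| | Crude test | Stratified by group (CMH) | Logistic: baseline HbA1c + group |
|---|---|---|---|
| Type I error, weak group effects | 4.5% | 4.7% | 4.9% |
| Type I error, strong group effects | 3.8% | 4.7% | 4.5% |
| Power at a 0.12-point HbA1c difference, weak | 54% | 54% | 59% |
| Power at a 0.12-point HbA1c difference, strong | 49% | 53% | 55% |

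The crude test does not exceed its nominal level. The full adjustment gains 59 − 54 = 5 and 55 − 49 = 6 points. Stratifying by group alone gains 0 to 4 points. Simulation error on a single power figure is about √(0.54 × 0.46/1500) = 1.3 points.

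**Step 2: sensitivity to the residual SD.** This is a separate simulation: 2760 vs 552, true difference 0.1 points, baseline truncated normal with mean 7.3 and SD 0.7, 400 trials per setting.
- SD 0.6: power 55% to 69%, a gain of 14 points. The squared ratio of mean z statistics is 1.30–1.33.
- SD 0.8: squared ratio 1.14–1.17.
- SD 1.0: power 33% to 35%, a gain of 2 points. Squared ratio 1.09–1.11.

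The only SD in the article is 1 (Sample size estimations). A residual SD after adjusting for baseline could be lower, but nothing in the article supports 0.6. Both simulations concern the 6.5% goal; the three HbA1c-reduction goals were not simulated.

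**Step 3: cost of Fisher's test.** Exact calculation at 2760 vs 552, nominal 5%, assumed event rates 3–20%: size 4.2–4.7% for Fisher and 4.9–5.0% for chi-square. Power is 75.7% vs 77.2% for 10% vs 14%, and 75.5% vs 77.3% for 5% vs 8%. The loss is under 2 points.

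**Step 4: patients already at goal.** Assume a share q is at or below 6.5% at visit 2, that 90% of them respond in either arm, and that 35% (metformin) and 42% (combination) of the others respond. The difference is then (1 − q) × 7.0 points. Power is Φ[(d − 1.96·SE₀)/SE₁], with SE₀ pooled and SE₁ unpooled, at 460 and 2300 patients.

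| q | Rates | Difference (points) | Power |
|---|---|---|---|
| 0 | 35.0% vs 42.0% | 7.0 | 80% |
| 5% | 37.8% vs 44.4% | 6.7 | 75% |
| 10% | 40.5% vs 46.8% | 6.3 | 70% |
| 20% | 46.0% vs 51.6% | 5.6 | 59% |

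For q = 10%: (0.063 − 1.96 × 0.02545)/0.02514 = 0.52, and Φ(0.52) = 0.70.

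Restricting to patients above 6.5% does not return the full 80%, because patients are lost. With q = 10%, 414 and 2070 remain. SE₀ = 0.02510/√0.9 = 0.02646 and SE₁ = 0.02450/√0.9 = 0.02583, so (0.070 − 1.96 × 0.02646)/0.02583 = 0.70 and power is 76%.

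The true q cannot be found from the article. With the step 2 baseline and visit-to-visit variation of SD 0.3, it is 5.3% with no lead-in change and 8.0% with a fall of 0.1 points.

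**The case against.** A chi-square test is a conventional choice for secondary responder percentages, and here it is sound. Because allocation is 5:1 inside every group, the groups are balanced between arms by design. A reader might infer from the randomization scheme that the crude tests are biased or inflate type I error. They do neither; if anything they are slightly conservative. Nor are the age/BMI groups ignored, since subgroup analyses of the efficacy endpoints are planned. This part of the objection stands in full.

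The responder and GI tests are also outside the sequential and Hochberg procedure, which covers only HbA1c non-inferiority overall and in the subgroups, so no confirmatory claim rests on them. The Fisher penalty is negligible, and baseline HbA1c has no evident role in a GI-event comparison. These points stand too and keep the weight low.

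A further objection is that an article may leave covariates and sensitivity analyses to the analysis plan; even the ANCOVA covariates are not listed. That holds for the handling of patients already at goal, which is therefore only a suggestion. It does not dispose of the main point, because the article names the tests and both are unadjusted.

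A reader might also infer that patients starting at 6.5% or below are simply scored as successes and flatter the combination. The article does not say so. Success is judged at the study endpoint, so such patients count only if still at goal then, and the rule is the same in both arms. It may raise both rates, but it shrinks the contrast. The three HbA1c-reduction goals and the GI test are untouched.

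**Conclusion.** The concern holds as a low-severity efficiency point on secondary and safety analyses. The tests are valid. For the 6.5% responder goal they forgo about 5–6 power points at an assumed residual SD of 0.8, with a range of roughly 2 (SD 1.0) to 14 (SD 0.6). The upper end has no support in the article. For GI events, the documents give no basis for sizing the gain from stratification.

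Possible dilution of the two 6.5% endpoints by patients already at goal follows from the entry range and the lead-in, but its size is unknown. At assumed shares of 5–10% it would take 0.3–0.7 points off a 7-point difference.

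The abstract's inequality, read literally, describes HbA1c below 6.5% and contradicts Subjects and the Discussion. It is most likely a reversed sign. It is a separate clerical matter, has no bearing on the choice of test, and is not evidence that such patients would be enrolled.

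**What to change.** 1. Make the main responder comparison a logistic regression on treatment, visit 2 HbA1c and age/BMI group, and report a standardized risk difference with a 95% confidence interval. The chi-square test can stay as a supportive analysis.
2. Compare the incidence of any GI event with a Mantel-Haenszel test and risk difference stratified by age/BMI group.
3. For the two goals based on 6.5%, add a supportive analysis in patients with visit 2 HbA1c above 6.5%. The restriction uses a value measured before treatment, so it keeps the randomized comparison. Report the number at or below 6.5% at visit 2 by arm.
4. Separately, reconcile the abstract's inequality with the range in Subjects and the Discussion, and state whether 6.5% itself is eligible.

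The cost is wording only. Every variable is already collected under Table 3, and no visit, sample size or primary analysis changes.

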### Sample size estimations

Non-inferiority testing will be performed on the subgroups of patients based on age and BMI. Assuming a treatment group difference of 0, standard deviation of 1, and a non-inferiority margin of 0.5, 690 patients will provide 90% power at a 1-sided with significance level of 0.05. Allowing for a 20% dropout rate, the number of subjects required for randomization is 690/ (1+20%) = 828 patients, yielding a total of 4 × 828 = 3312 subjects. For the estimation of the sample size, nQuery Advisor®, version 7.0, will be used.

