### Data analysis

Intention-to-treat (ITT) analysis will be performed. The full analysis set (FAS) will include all randomized patients who took the study drugs at least once and had at least 1 primary or secondary efficacy evaluation after baseline. For assessment of missing primary efficacy variables, the last observation carried forward (LOCF) technique will be used. The per-protocol set (PPS) will include ITT patients completing at least 22 weeks of treatment, and those who discontinued the study due to a poor therapeutic response (FPG >13.3 mmol/L [240 mg/dL]) after 12 weeks of treatment, provided they have no major protocol deviations and had a valid assessment of HbA1c levels within 7 days after their last dose of study drug. Any major deviation from the protocol will be identified and documented in the analysis plan. Patients will be analyzed in the treatment group to which they were randomly assigned for the efficacy assessment.

The safety analysis set (SAS) will include patients who took the study drugs at least once and had at least 1 safety assessment after baseline. The safety analyses will be according to the patients’ treatment, and will include the description of any AEs.

The FAS set will be used as the primary population for the primary efficacy variable, the change from baseline in HbA1c levels at 24 weeks. The primary efficacy variable will be analyzed using an analysis of covariance (ANCOVA) model and the LOCF approach.

Non-inferiority of the study drug will be analyzed using the null hypothesis and a unilateral alternative hypothesis, which are defined as follows:

$$H_{0},\delta_{\mathrm{vildagliptin}}\geq \delta_{\mathrm{metformin}}+0.3\%$$

$$H_{a},\delta_{\mathrm{vildagliptin}}<\delta_{\mathrm{metformin}}+0.3\%$$

where δ represents the change from baseline.

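### The sample size section states a non-inferiority margin of 0.5, but the hypotheses use 0.3% and the 690 patients per subgroup reproduce only with 0.3

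*Protocol article*

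**What the plan says.** The Data analysis section of the protocol article writes the null and alternative hypotheses for change from baseline in HbA1c with the boundary at "\delta_{\mathrm{metformin}}+0.3" percent. It then describes a sequence: non-inferiority is tested in the overall population first and, if shown, in the four age/BMI subgroups with a Hochberg procedure. It mentions no change of margin between the two steps.

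The Sample size estimations section says that it concerns the subgroup non-inferiority tests and continues: "Assuming a treatment group difference of 0, standard deviation of 1, and a non-inferiority margin of 0.5, 690 patients will provide 90% power", with the test "at a 1-sided with significance level of 0.05". The 690 is then raised to 828 for dropout and multiplied by four to give 3312.

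Table 2 lists non-inferiority in change from baseline in HbA1c as the primary objective for the whole population and as a secondary objective for the subgroups. The endpoint is the same in both. The Study design section gives 5:1 randomization within each subgroup.

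**The concern.** One endpoint and one type of test carry two margins, 0.3% and 0.5, which differ by 0.2 percentage points of HbA1c (0.2/0.3 = 67% of the smaller value). In a non-inferiority trial the margin is the decision threshold. Because the sample size section opens with the subgroup tests, a reader could take 0.5 as the subgroup margin, although the hypotheses are stated without any such restriction.

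Two things are at stake. First, a subgroup result with an upper confidence limit between 0.3% and 0.5% would pass under one section and fail under the other. The trial is open-label, so the choice should be settled in writing before results are known. Second, the power statement cannot be reproduced from the inputs printed beside it, which leaves the reader unsure which input is wrong.

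**Working it through.** **Inputs.** True difference 0, SD 1, 90% power and one-sided alpha 0.05 come from Sample size estimations. The 5:1 allocation within each subgroup comes from Study design. The margin is 0.5 (Sample size estimations) or 0.3 (hypotheses in Data analysis).

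**Formula.** With n controls and 5n on the combination, and true difference 0:

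n = (1 + 1/5) × SD² × (z₀.₉₅ + z₀.₉₀)² / margin², total = 6n

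Here (1.645 + 1.282)² = 8.564 from unrounded quantiles, so n = 1.2 × 8.564 / margin² = 10.277 / margin².

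**Attempt to reproduce 690 with the printed margin, 0.5.** n = 10.277 / 0.25 = 41.1, rounded up to 42. The total is 42 + 210 = 252. The noncentral t gives the same 252. The stated 690 is 690/252 = 2.7 times larger.

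**With the margin in the hypotheses, 0.3.** n = 10.277 / 0.09 = 114.2, rounded up to 115. The total is 115 + 575 = 690, exactly the stated figure. The noncentral t again gives 115 + 575. One control fewer (114:570) gives 89.9%, so 690 is the smallest 5:1 total that reaches 90%.

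**Power of 690 patients (575:115).** The standard error is √(1/115 + 1/575) = 0.102.

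| Margin | margin/SE − 1.645 | Power, normal | Power, noncentral t |
|---|---|---|---|
| 0.3 | 2.937 − 1.645 = 1.292 | 90.2% | 90.1% |
| 0.5 | 4.895 − 1.645 = 3.250 | 99.9% | 99.9% |

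**Can another reading rescue 0.5?** Totals at margin 0.5 (normal formula, rounded up per arm):

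| One-sided alpha | 5:1 | 1:1 |
|---|---|---|
| 0.05 | 252 | 138 |
| 0.025 | 306 | 170 |
| 0.0125 | 360 | 200 |
| 0.00625 | 414 | 230 |

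None is near 690. A margin of 0.4 does not give 690 under any of these settings either (largest total 648). Among margins 0.3, 0.4 and 0.5, both ratios and all four alphas, only 0.3 with 5:1 and one-sided 0.05 yields 690. Solved backwards, 575:115 with 90% power implies a margin of 2.926 × 0.102 = 0.299. Keeping 0.5 would require an SD of 0.5/0.299 = 1.67 instead of the stated 1.

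**What the ambiguity means for a subgroup result.** At 575:115 and SD 1, the one-sided 95% half-width is 1.645 × 0.102 = 0.168. An observed difference between 0.3 − 0.168 = 0.13 and 0.5 − 0.168 = 0.33 would fail at 0.3 and pass at 0.5. If the true difference were 0.3, which the hypotheses count as unacceptable, a 0.5 margin would declare non-inferiority with probability Φ(0.2/0.102 − 1.645) = Φ(0.31), about 62%, against 5% at a margin of 0.3.

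**The case against.** The strongest reply is that the error has little practical effect. The value 0.5 appears only in the sample size section, which is framed around the subgroups. The primary test is defined by formal hypotheses with 0.3%, and nothing attaches 0.5 to it. The subgroup tests are secondary and follow only after overall success. A power statement lists planning assumptions, and a formal hypothesis would normally prevail over it. The number of patients fits the stricter margin, so the trial is not undersized through this error. That 690 was derived from 0.3 is also an inference: no sentence excludes a separate subgroup margin.

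Much of this stands. The ambiguity bears mainly on the four subgroup tests, and correcting the margin changes neither the sample size nor the power at 0.3%. It does not remove the point. The subgroup tests are part of the formal error-controlled sequence, and the trial was sized for them, so their threshold must be as clear as the primary one. A deliberate 0.5 margin for the subgroups would leave the 690 unexplained. The inference to 0.3 rests on an exact match under every other stated input.

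**Conclusion.** The concern holds and should be corrected before analysis. The margin of 0.5 contradicts the 0.3% in the hypotheses and does not produce the stated 690 or the stated 90% power: at 0.5 the requirement is 252 per subgroup, and 690 gives 99.9%. At 0.3 the requirement is exactly 690, with 90.1% power. The conclusion assumes that the SD, true difference, alpha, power and 5:1 ratio are as printed and that each arm is rounded up to whole patients. Without rounding up, the normal formula gives a total of about 685, which does not alter the conclusion. The error affects the decision threshold and the reproducibility of the calculation; it does not affect the 690 itself.

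**What to change.** In Sample size estimations, change the margin from 0.5 to 0.3 and give the split behind the 690 (575 combination, 115 metformin), so that the calculation can be reproduced where it stands. In Data analysis, add one sentence stating that 0.3% is the non-inferiority margin for the overall test and for each of the four subgroup tests. The sponsor should confirm from its sample size records that 0.3 was the input. If 0.5 was really meant for the subgroups, the protocol must say so, justify it and replace the 690.

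The cost is one corrected figure and one added sentence, with no change in patients on this account. The dropout step needs separate attention: as printed, 690/(1 + 20%) equals 575, whereas 828 is 690 × 1.2. Correcting the margin does not settle that.

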	• To demonstrate that the change from baseline in HbA1c levels after 24 weeks of treatment with vildagliptin 50 mg bid as add-on therapy to metformin 500 mg bid is non-inferior to high-dose metformin
**2.**	**Secondary objectives:**
	• To demonstrate in predefined patient subgroups [based on body mass index (BMI <24 and ≥24 kg/m^2^) and age (<60 and ≥60 years)] that vildagliptin add-on therapy to metformin is non-inferior to high-dose metformin in the change from baseline in HbA1c levels
	• To determine the percentages of patients achieving the target HbA1c level of ≤6.5% in the two treatment arms of the overall population and in the predefined subgroups
	• To determine the percentages of patients achieving the target HbA1c level of ≤6.5% in the two treatment arms of the overall population and in the predefined subgroups
	• To determine the mean change from baseline to 24 weeks in fasting plasma glucose in the overall population and in the predefined subgroups
	• To determine the mean change from baseline to 24 weeks in 2-hour postprandial glucose in a subsample of 464 patients with type 2 diabetes mellitus
	• Safety analysis
**3.**	**Exploratory objectives:**
	• To determine the mean change from baseline to 24 weeks in body weight and lipid parameters in the overall population and in the predefined subgroups
	• To determine the change from baseline to 24 weeks in β-cell function in a subsample of 464 patients with type 2 diabetes mellitus

BMI: body mass index; HbA1c: glycated hemoglobin.

Treatment will also be discontinued if the patient cannot tolerate the GI symptoms associated with a dose increase at visit 2. If patients in Group B cannot tolerate the GI symptoms at visit 3, the dose of metformin can be decreased by one tablet (250 mg) until the GI symptoms improve. After that, the dose will be gradually increased over 1–2 weeks. The dose of the metformin in Group B will be at least 500 mg bid until week 12. After week 12 (visit 4), dose adjustments of metformin will not be allowed at any time. Adjustment of the vildagliptin dose will not be allowed throughout the study.

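### The stated 90% power is for one subgroup tested alone, not for the planned Hochberg test of four subgroups (about 88% per subgroup at the 0.3 margin)

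*Protocol article*

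**What the plan says.** - **Sample size estimations.** The calculation is for the subgroup non-inferiority tests. Its inputs are "Assuming a treatment group difference of 0, standard deviation of 1" and "a non-inferiority margin of 0.5", and its result is "690 patients will provide 90% power at a 1-sided with significance level of 0.05". After a 20% dropout allowance this becomes 828 per subgroup, "yielding a total of 4 × 828 = 3312 subjects".
- **Data analysis, hypotheses.** The one-sided non-inferiority hypotheses use a margin of 0.3% HbA1c, not 0.5.
- **Data analysis, multiplicity.** To hold overall type I error at 0.05, "a sequential test procedure along with the Hochberg procedure will be employed". The overall population is tested first. If it passes, the four subgroups are tested.
- **Table 2.** Subgroup non-inferiority is a secondary objective, introduced by "To demonstrate in predefined patient subgroups". Nothing says that all four subgroups must succeed.
- **Study design.** Randomization is 5:1 within each subgroup.
- **Data analysis, populations.** The primary set is the full analysis set (FAS), with the last observation carried forward (LOCF).

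**The concern.** The only power figure in the article belongs to a test that will not be run in that form. Under Hochberg a subgroup is judged at the full 0.05 only when all four p-values are at or below 0.05. Otherwise the threshold is 0.025, 0.0167 or 0.0125. The subgroup tests determine the size of the trial, so the stated power should describe the procedure that will be applied to them.

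A second matter concerns interpretation. The trial's distinctive question is whether the benefit varies with age and BMI. If three subgroups pass and one does not, that could be taken for an age or BMI effect. A reader needs to know how often such a pattern arises by chance when the treatments are equal everywhere, and the article gives no figure for this.

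**Working it through.** **Inputs.** SD 1, true difference 0, one-sided 0.05, 90% power, 690 per subgroup, 828 randomized per subgroup (all Sample size estimations); 5:1 allocation (Study design); margin 0.3 (Data analysis) or 0.5 (Sample size estimations).

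**1. Reproduce the 690.** Control patients = (1 + 1/5) × (1.645 + 1.282)² / margin².
- Margin 0.3: 1.2 × 8.564 / 0.09 = 114.2, rounded up to 115. With 575 on the combination, the total is 690, an exact match.
- Margin 0.5: 1.2 × 8.564 / 0.25 = 41.1, rounded up to 42, total 252. No match.

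The published 690 and 90% therefore imply a margin of 0.3.

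**2. Power of one subgroup tested alone.** SE = √(1/115 + 1/575) = 0.10215.
- Margin 0.3: Φ(0.3/0.10215 − 1.645) = Φ(1.292) = 90.2%.
- Margin 0.5: Φ(0.5/0.10215 − 1.645) = Φ(3.250) = 99.9%.

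**3. Power under Hochberg.** One million trials were simulated, each with four independent z-statistics of mean 0.3/SE and variance 1, applying Hochberg at one-sided 0.05. With 690 analysed per subgroup, average power per subgroup is 88.2%, at least one subgroup succeeds in 99.7% of trials, and at least three succeed in 89.1%.

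The last figure can be checked by hand. Exactly three succeed when one p-value exceeds 0.05 and the other three are at most 0.025. Power at 0.025 is 83.6%, so this has probability 4 × (1 − 0.9018) × 0.8357³ = 22.9%. Adding the 66.1% from step 4 gives 89.1% within rounding.

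**4. All four succeed.** Hochberg rejects all four hypotheses exactly when the largest p-value is at most 0.05. The subgroups share no patients, so the probability is the single-test power to the fourth power: 0.9018⁴ = 66.1%. The simulation gave 66.3%.

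**5. Range over the number analysed, margin 0.3.**

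| Analysed per subgroup | SE | One test alone | Per subgroup, Hochberg | All four |
|---|---|---|---|---|
| 662 (80% of 828) | 0.10426 | 89.1% | 86.7% | 63.1% |
| 690 | 0.10215 | 90.2% | 88.2% | 66.1% |
| 828 (all, through LOCF) | 0.09325 | 94.2% | 93.4% | 78.8% |

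The first row is below 690 because 828 is 690 × 1.2, and losing 20% of 828 leaves 662.

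**6. The same at margin 0.5, 690 analysed.** 99.9% per subgroup under Hochberg and 99.8% for all four.

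**7. The preceding overall test.** With 460 control patients (4 × 115), its power at margin 0.3 exceeds 99.99%. Requiring it to pass first leaves the all-four figure at 66.1%.

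**The case against.** The strongest reply is that no stated figure is wrong. The section visibly derives 690 for one subgroup and multiplies by four, so a careful reader can see that 90% is per subgroup, and no joint power is claimed. Sizing each subgroup at 90% is a legitimate choice. Choosing Hochberg suggests that each subgroup claim is meant to stand alone: if all four had to succeed, each could be tested at 0.05 without adjustment. For separate claims, the relevant figures are the 88% per subgroup or the 99.7% for at least one. The loss from 90% to 88% is small, and if LOCF keeps all 828 patients the Hochberg power is 93%, above the stated figure. The subgroup tests are secondary, and a condensed article may leave joint power to the full protocol.

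Most of this stands, and it limits the point to the description of power.

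- A reader might infer that Hochberg lowers the power from 90% to 66%. It does not. The 66% is the product of four independent tests and would be the same with no adjustment.
- A reader might infer that the subgroup objective has only a 66% chance of success. The documents do not support this, because no section defines success as all four.
- The 66% also assumes a true difference of exactly 0. The Discussion cites a trial of a similar comparison in which the combination reduced HbA1c more. As an illustration only, an assumed true advantage of 0.1 gives Φ(0.4/0.10215 − 1.645) = 98.8% for one subgroup tested alone and 0.988⁴ = 95% for all four.

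What the reply does not remove is that the printed 90% belongs to a single unadjusted test, while the plan specifies a different procedure. The figure also sits beside a margin that does not produce it.

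**Conclusion.** The point holds in a limited form. The stated 90% is not the power of the planned procedure under either margin: about 88% per subgroup at 0.3 with 690 analysed (87% to 93% over 662 to 828), and 99.9% at 0.5. The conflict between 0.3 and 0.5 is the firmer error and has to be settled first; if 0.5 were truly intended, the concern about insufficient power would vanish.

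At 0.3, with identical treatments in every subgroup, all four succeed in about 66% of trials (63% to 79%). At least one therefore misses non-inferiority in about 34% (21% to 37%). This is an operating characteristic worth stating, not a misprinted number.

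These figures rest on SD 1, true difference 0, one-sided 0.05, 5:1 allocation and equal subgroup sizes. They do not show that the trial is too small or that the primary test is affected.

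**What to change.** Reconcile the margin between Sample size estimations and Data analysis. Then restate the power for the procedure to be used. If the margin is 0.3, give about 88% per subgroup under Hochberg with 690 analysed (87% with 80% of 828, 93% with all 828) and, beside it, about 66% (63% to 79%) for all four. Add that one subgroup missing non-inferiority is not in itself evidence that the effect depends on age or BMI.

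The sample size stays as it is. Once the margin is settled, the cost is a sentence or two and, at 690 analysed, a slightly less favourable headline figure.
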